## Abstract

**Background:**

Safety measures should be applied to reduce work-related fatal and non-fatal fall injuries. However, according to the labor inspectorate, more than 80% of Dutch construction sites violate safety regulations for working from heights. To increase compliance with safety regulations, employers and workers have to select, implement and monitor safety measures. To facilitate this behavioral change, stimulating knowledge awareness and personalized feedback are frequently advocated behavior change techniques. For this study, two behavior change strategies have been developed in addition to the announcement of safety inspections by the labor inspectorate. These strategies consist of 1) face-to-face contacts with safety consultants and 2) direct mail with access to internet facilities. The objective of this study is to evaluate the effectiveness of these two strategies on the safety violations for working from heights, the process and the cost measures.

**Methods/Design:**

This study is a block randomized intervention trial in 27 cities to establish the effects of the face-to-face guidance strategy (N = 9), a direct mailing strategy (N = 9) and a control condition of no guidance (N = 9) on safety violations to record by labor inspectors after three months. A process evaluation for both strategies will be performed to determine program implementation (reach, dose delivered and dose received), satisfaction, knowledge and perceived safety behavior. A cost analysis will be performed to establish the financial costs for both strategies. The present study is in accordance with the CONSORT statement.

**Discussion:**

This study increases insight into performing practice-based randomized controlled trials. The outcome will help to evaluate the effect of two guidance strategies on safety violations. If these strategies are effective, implementation of these strategies through the national institute of safety and health or labor inspectorate can take place to guide construction companies in complying with safety regulations.

**Trial registration:**

NTR 4298 on 29-nov-2013.

## Background

Worldwide, occupational diseases and injuries frequently occur and are consequences of exposures exceeding biological tolerances of humans. The burden of occupational diseases and injuries is high, especially in the construction industry [1,2]. Construction workers are frequently exposed to various types of injury-inducing hazards, especially falling from heights [3]. In principle, occupational diseases [4-6] and occupational injuries can be prevented by means of control measures at worksites.

In the construction industry – as in many other industrial sectors – the majority of control measures are not evaluated in terms of reductions in injuries [7,8]. The reality in daily practice is that work-related injuries occur too infrequently to set up (randomized) controlled intervention studies with injuries as primary outcome measure. In addition, it is difficult and costly to effectively intervene across a large enough construction population. The present randomized controlled intervention study focuses on a more frequently occurring outcome measure like safety violations in the construction industry, accompanied by process measures to get insight in the implementation to evaluate the effect of two strategies.

According to the labor inspectorate (personal communication), more than 80% of Dutch construction sites violate safety regulations for working from heights, while 14% of the construction workers report that unsafe situations prevail at work [9]. Safety measures should be applied to reduce work-related fatal and non-fatal fall injuries. To increase compliance with safety regulations, employers and workers need to select, implement and monitor safety measures. To facilitate this behavioral change [10], stimulating knowledge awareness (e.g. Leeman et al. [11]) and personalized feedback (e.g. Diclemente et al. [12]) are behavior change techniques that are frequently advocated.

For this study, two behavior change strategies have been developed to reduce the number of safety violations concerning the installation and use of rolling scaffolds, ladders and stairs, in addition to the announcement of safety inspections by the labor inspectorate. These strategies are based on aspects of awareness-raising and personalized feedback and consist of 1) face-to-face contacts with safety consultants and 2) direct mail with internet links.

### Study objectives

The objective of this study is to evaluate the effectiveness of a face-to-face strategy and a direct mail strategy on safety violations for working from heights among construction companies compared to the control condition of only the announcement of safety inspections by the labor inspectorate. For both guidance strategies, a process and cost evaluation will be performed.

### Hypothesis

We hypothesize that both guidance strategies will reduce safety violations with rolling scaffolds, ladders and stairs compared to the control condition of a general announcement of inspection in construction companies. In addition, the face-to-face strategy is thought to be superior to the direct mail strategy. This is expected to be due to a higher impact of personalized feedback in the face-to-face guidance strategy on executing safety measures within the construction companies compared with awareness-raising in the direct mail strategy. The financial costs are expected to be higher in the face-to-face guidance strategy, especially due to hiring safety consultants and their coordinator for work site visits.

## Methods/Design

In a three-armed block randomized controlled trial (RCT), 27 large cities has been stratified within three regions in the Netherlands (North-East, West, South) and each city has been assigned to one of two intervention groups or the control group using nQuery Advisor® Version 7.0. As a result of the inspection procedure of the Dutch labor inspectorate, i.e. unannounced work site inspections in a well-defined area and time period in the Netherlands, the interventions take place at construction companies working in larger cities.

For the description of the design of the safety intervention and the two guidance strategies, we follow the CONSORT statement [13].

### Study design

A randomized intervention trial is performed to compare the effectiveness of two behavior change strategies, a face-to-face guidance strategy and a direct mailing strategy, with a control condition. A process evaluation and a cost evaluation will take place for both guidance strategies.

The study protocol does not meet the criteria of the “Act medical-scientific research with human participants”, i.e. not a study of a medical nature and the subjects receive not a particular treatment or are asked to behave in a particular way [14]. Therefore, the Medical Ethics Committee of the Academic Medical Center Amsterdam (AMC) has not been asked for approval of the study protocol.

### Setting

The guidance strategies will be given to construction companies. Inclusion criteria of the construction companies are: 1) involved in the painting and maintenance of buildings and 2) working in one of the 18 pre-randomized bigger cities in the Netherlands during May 2014.

### Study population

The research population includes all construction sites of the participating companies.

### Recruitment of participants

Two methods for recruiting the construction companies will be used. First of all, a call centre will contact potential eligible companies located in an area within 50 kilometers of one of the 18 pre-randomized cities and companies with at least 15 workers who are expected to work in a wider area in the Netherlands. The second method of recruitment consists of publishing a call-up with a description of the project in the employers’ newsletter and the website and newsletter of the national organization for safety and health (Arbouw). Construction companies willing to participate are contacted by Arbouw for further arrangements concerning the proposed interventions. Employers and workers will formally be asked for their consent when sending the questionnaires.

### Interventions

The safety measures within the two guidance strategies are based on the inspection module of the labor inspectorate and guidelines of the Dutch construction safety and health institute Arbouw.

#### Face-to-face guidance strategy

The face-to-face guidance strategy consists of personal advice at construction companies with a maximum of three visits in which workers are informed about preventing falling hazards with rolling scaffolds, ladders and stairs. The employer or contact person of each construction company is encouraged to involve all their workers in the selection, use and monitoring of safety measures to reduce falling hazards when working with rolling scaffolds, ladders and stairs.

Company visits will take place at the company or at work sites on dates and times agreed on with the contact person of each company during a three-month period. The number of company visits will depend on the size of the company; one visit when <5 workers, two visits when 5–15 workers, and three visits when > 15 workers. It is advisable to contact management and the workers’ council when planning company visits.

Each visit consists of a one- to two-hour interactive consultancy meeting with the contact person and workers of the construction company. Information is exchanged concerning selection, implementation and monitoring of safety measures with regard to rolling scaffolds, ladders and stairs. The safety consultant writes a short report of the findings and the advised safety measures. A maximum of five types of advice can be given, and advice can be added in subsequent visits to the same company. In a company report, advice is grouped into i) the choice and suitability of the equipment for working from heights (i.e. rolling scaffolds, ladders and stairs), ii) safety measures for risk control when using equipment for working from heights, iii) teaching and training, iv) supervising on the selection and safety use of equipment for working from heights, v) remaining advice for improving safe and healthy workplaces.

In total, six safety consultants, experienced in equipment for working from heights, are involved in the face-to-face strategy. In a meeting, these consultants are informed about documented safety measures in the inspection module of the labor inspectorate, safety protocols of employers’ organization providing equipment for working from heights, and two guidelines of Arbouw concerning safe use of rolling scaffolds, and ladders and stairs.

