### Process evaluation

The process evaluation of the two guidance strategies will be determined using indicators as defined by Linnan and Steckler [15], Murta et al. [16] and Bowen et al. [17]. The following indicators for implementation of the program will be evaluated [15,16]: reach, dose delivered, dose received. Satisfaction with the intervention (score 0–10), increase in perceived knowledge on safety measures (score 0–10) and perceived effectiveness on safety behavior (score 0–10) are used as indicators for acceptability concerning the interventions [17].

Reach is defined as the attendance rate of the construction companies at the intervention. Attendance rate is defined as the number of construction companies participating in this study relative to the number of eligible construction companies invited through the recruitment strategies. The attendance will be assessed by means of a logbook during the recruitment of the construction companies. Construction companies that do not participate will be asked to explain why.

Dose delivered refers to the proportion of the intended intervention that is actually delivered to the participating contact persons of the construction companies. For the face-to-face guidance strategy, the number of company visits and company reports including advice delivered by the safety consultants to the contact person of the construction companies will be assessed by means of a logbook filled in by the safety consultants and checked by Arbouw, who coordinate the company visits as applied by the safety consultants. For the direct mailing strategy, dose delivered will be assessed by means of the number of direct postal mails and emails to the contact person of the construction companies. The dose delivered is rated as sufficient when more than 90% of the companies receive the interventions (i.e. visit of the safety consultant and postal information).

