Effect on working safely with rolling scaffolds, ladders and stairs as a result of the intervention is measured by asking the employers and workers to what extent the perceived effect on safety behavior is rated (0–10, 0 = no effect, 10 = large effect). The rates are defined as poor (<6), moderate (≥6 and <7.5) or good (≥7.5).

The process outcomes will be measured after the intervention period through questionnaires sent to the companies and their workers.

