### Randomization

The stratified allocation of the cities (nine cities in each of the three regions) to the intervention groups or to the control group will be performed using a random, computerized allocation procedure. The primary researcher (HM) blindly randomizes the groups for the 27 cities. The safety consultants who execute the face-to-face strategy are assigned by Arbouw.

The intervention and implementation strategy makes blind group assignment of the construction companies, consultants and Arbouw impossible.

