### Statistical analyses

The primary outcome measures, i.e. ascertained safety violations, will be presented for the two guidance strategies and the control condition using descriptive statistics. The number of safety violations concerning the installing and use of equipment for working from heights at worksites of painting and maintenance companies ascertained by the Dutch labor inspectorate in the included 27 cities during three weeks in May 2014 will be retrieved by the primary researcher (HM) from the database of the Dutch labor inspectorate. Differences in the mean number of safety violations will be tested using an analysis of variance.

The three process measurements (i.e. satisfaction, insight and safe working behavior) of both intervention strategies are post-tested and converted into continuous variables on a scale of 0–100. The differences between both interventions are examined using independent t-tests.

The analysis is performed on an intention-to-treat basis. IBM SPSS 19.0 will be used for the statistical tests. Statistical significance is defined as p < 0.05 for all outcome measures.

The costs calculation for each intervention strategy will be analyzed descriptively.

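### The t-tests comparing process scores between face-to-face and direct mail ignore the six shared consultants and the randomised cities, so their standard errors are likely too small

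*Protocol article*

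**What the plan says.** Under Face-to-face guidance strategy, guidance is given in personal meetings of one to two hours, one to three per company depending on its size, and the staffing is fixed: "In total, six safety consultants, experienced in equipment for working from heights, are involved in the face-to-face strategy". Under Randomization, "The safety consultants who execute the face-to-face strategy are assigned by Arbouw"; no map of consultants to companies or cities is given. The Abstract allots nine cities to each of the three conditions, and Randomization stratifies the 27 cities by region.

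Under Process evaluation, employers and workers rate satisfaction, gain in knowledge and perceived effect on safe working: "The process outcomes will be measured after the intervention period through questionnaires sent to the companies and their workers". The number of visits and reports is "assessed by means of a logbook filled in by the safety consultants and checked by Arbouw".

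Under Statistical analyses, "The three process measurements (i.e. satisfaction, insight and safe working behavior) of both intervention strategies are post-tested", and then "The differences between both interventions are examined using independent t-tests". No term for consultant, company or city is named. The primary outcome is handled separately: "Differences in the mean number of safety violations will be tested using an analysis of variance".

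**The concern.** An independent t-test assumes that every score is independent of every other. Two features of the design work against this. Cities, not companies or respondents, were randomised, which affects both arms. In the face-to-face arm the scores are also ratings of a consultation, and six people gave all of those consultations. Once more than six companies take part, some must share a consultant, and their ratings may rise or fall together. Direct mail is a standard package with no individual deliverer, so this second source exists in one arm only.

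The consultant layer deserves its own mention because averaging by company does not remove it, and averaging by city may not either. If all nine face-to-face cities have visited companies, six consultants cannot each keep to a separate city, so at least one covers two or more.

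What is at stake is the comparison of acceptability and perceived effect. A few unusually strong or weak consultants could be reported, with an overconfident p-value, as a difference between the strategies.

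**Working it through.** **Inputs from the article.** Six consultants; nine cities per arm; independent t-tests; significance at p < 0.05.

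**Inputs that must be assumed.** The number of companies answering per arm (30, 60 or 90) and the consultant intraclass correlation ρ (0.05, 0.10 or 0.20). The article states neither. Its 64 locations per group is a count of inspected sites for the primary outcome, not of questionnaire respondents, so there is no figure of the plan's own to reproduce here. The article also does not say whether the t-tests use respondents or companies; one mean score per company is assumed, which favours the plan.

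**Company-level test.** With n companies per arm split evenly, each consultant has m = n/6 companies. The variance of the face-to-face mean is inflated by DE = 1 + (m − 1)ρ; direct mail is not inflated by consultants. With equal total variances, the true standard error divided by the t-test standard error is √((DE + 1)/2). The false-positive rate is approximately 2 × [1 − Φ(1.96 / ratio)].

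Example, n = 60 and ρ = 0.10: m = 10; DE = 1 + 9 × 0.10 = 1.90; ratio = √(2.90/2) = 1.204; 1.96/1.204 = 1.628; false-positive rate about 10.4%.

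| Companies per arm | ρ | DE | SE ratio | False positives, formula | False positives, simulated |
|---|---|---|---|---|---|
| 30 | 0.05 | 1.20 | 1.049 | 6.2% | 6.2% |
| 30 | 0.10 | 1.40 | 1.095 | 7.4% | 7.6% |
| 30 | 0.20 | 1.80 | 1.183 | 9.8% | 10.3% |
| 60 | 0.05 | 1.45 | 1.107 | 7.7% | 7.9% |
| 60 | 0.10 | 1.90 | 1.204 | 10.4% | 10.0% |
| 60 | 0.20 | 2.80 | 1.378 | 15.5% | 15.4% |
| 90 | 0.05 | 1.70 | 1.162 | 9.2% | 9.3% |
| 90 | 0.10 | 2.40 | 1.304 | 13.3% | 13.5% |
| 90 | 0.20 | 3.80 | 1.549 | 20.6% | 20.7% |

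The simulations used 20,000 trials per setting, no true difference, and the consultant effect in the face-to-face arm only. At ρ = 0 the test holds its 5%.

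**City-level test.** Suppose nine city means per arm are compared, with three consultants serving two cities each and three serving one. For k companies per city:
- true variance of the face-to-face mean: 15ρ/81 + (1 − ρ)/(9k), where 15 = 3 × 2² + 3 × 1²;
- variance of one city mean: V = ρ + (1 − ρ)/k;
- what the t-test expects for the face-to-face mean: (1/8)(V − true variance of the mean);
- direct mail: 1/(9k) in both the true and the expected variance.

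For k = 8 and ρ = 0.20, the true face-to-face variance is 0.0370 + 0.0111 = 0.0481 and V = 0.30. The t-test expects (0.30 − 0.0481)/8 = 0.0315. Adding 1/72 = 0.0139 to each gives 0.0620 against 0.0454, an SE ratio of 1.17 and, on 16 degrees of freedom, about 9% false positives. For k = 4 and ρ = 0.05 the ratio is 1.035 and the rate just under 6%. Simulated rates over ρ = 0.05 to 0.20 were about 5–8% for k = 4 and 6–9% for k = 8.

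These figures isolate the consultant effect. Correlation within city, in both arms, is set to zero here and would add to the error.

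**The case against.** The strongest case on the other side is that this is minor. The t-tests cover self-ratings that the article uses as indicators of acceptability; no sample size or primary conclusion rests on them. The larger rates need 60 or 90 companies and a correlation of 0.20, none of which has a source in the article. Consultants share a briefing, the inspection module and guidelines, may give at most five types of advice and report in a fixed grouping, all of which should narrow differences between them. At 30 companies and ρ = 0.05 the rate is only 6.2%. A variance estimated from six consultants is imprecise, and treating them as a sample rather than as the programme delivered is a choice of inference target.

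All of this stands as a limit on size. It does not rescue the test: standardised content reduces the consultant correlation but does not make it zero, and the article names an analysis that assumes zero. Because the test itself is stated, this is not detail left to an analysis plan.

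Three stronger readings are tempting and not supported:
- A reader might infer that the test of the Hypothesis section, that face-to-face is superior to direct mail, is undermined by these t-tests. That hypothesis concerns safety violations, which are tested by analysis of variance.
- A reader might infer that the face-to-face arm has only six effective observations. At 30 companies and ρ = 0.05 the effective number is 30/1.20 = 25.
- A reader might take sharing of consultants across cities as stated. It is inferred from six being fewer than nine, and only if every face-to-face city has visited companies. Nor does the article say that one consultant makes all visits to a company.

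**Conclusion.** The point holds for the secondary process outcomes only. The stated t-tests ignore the randomised city in both arms and the consultant in the face-to-face arm, and their standard errors are too small for any positive consultant correlation. Under the assumed ranges the false-positive rate is about 6–10%, 8–15% or 9–21% with 30, 60 or 90 companies per arm, and about 5–9% for city means under the assumed pattern of sharing. The direction follows from the design; the size depends on company numbers and a correlation that the article does not give, and is slight if both are small. It is worth correcting because the correction is cheap.

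**What to change.** 1. From the logbook that the consultants already complete, record which consultant or consultants visited each face-to-face company.
2. Replace the independent t-tests by a mixed model on company mean scores, or on respondents with a random company effect. Include strategy and region as fixed effects, a random city effect in both arms, a random consultant effect in the face-to-face arm only, arm-specific residual variances and small-sample degrees of freedom. A consultant term alone would not do: direct mail companies would still be treated as independent although whole cities were allocated. Attach each company to the city through which it was allocated, and state how companies with more than one consultant are handled.
3. Report face-to-face means by consultant descriptively.
4. If the variance between six consultants cannot be estimated, say that the intervals apply to these six consultants only.

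The assignment of consultants need not change. The cost is one linked data field, a revised analysis paragraph and wider intervals for the process comparison.
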